## Abstract

**Background:**

There are variations in the management of patients with suspected pancreatic and periampullary cancers and/or malignant biliary obstruction. These differences may be due to a number of organizational, institutional, and patient factors that could affect outcomes for those with curable or incurable disease. The Receipt of Curative Resection or Palliative Care for Hepatopancreaticobiliary Tumours (RICOCHET) study will be the first to provide a snapshot of investigative pathways across the United Kingdom to reflect the real-world practice in these patients. The RICOCHET study is contemporary to new national and international clinical guidance and can potentially inform future local and national strategic planning to optimize care for patients with suspected hepatopancreaticobiliary (HPB) malignancies.

**Objective:**

The aim of this study is to define national variation in the investigative and management pathways of patients with suspected HPB malignancies and to determine the effect of these variations on patient outcomes.

**Methods:**

The RICOCHET study is a nationwide, multicenter, prospective study. It is led by trainees through collaboration between surgical and medical specialties. Patients with suspected pancreatic cancer, other periampullary cancer, or extrahepatic cholangiocarcinoma presenting to hospitals in the United Kingdom will be identified over 90 days. Each case will be followed up for 90 days to collect data on the mode of presentation, investigations, interventions, use of local and specialist multidisciplinary team meetings, and transfer of care between hub and spoke sites. Furthermore, the study will define dates and intervals between key points in the patient pathway.

**Results:**

The RICOCHET study results and analyses will be subject to peer review by presenting them at international cross-specialty conferences and by submitting them for publication in open-access journals. Moreover, our findings will be presented to patient groups and sponsoring charities (eg, Pancreatic Cancer UK), who in turn will disseminate key findings to the primary beneficiaries of the results: the patients. The RICOCHET study was funded in September 2017. Data collection started in April 2018 and the planned end date for data upload is spring 2019. Data analysis will take place in the summer of 2019 and the first results are expected to be published in late 2019 or early 2020.

**Conclusions:**

The RICOCHET study is a multidisciplinary, prospective, observational study that aims to highlight variability in practice and to determine whether these affect the outcomes of patients with HPB malignancies. This is a trainee-led initiative that utilizes a novel design to achieve full coverage of the differences in diagnostic and management pathways. The RICOCHET study may provide evidence to develop a more standardized approach to managing patients with suspected HPB malignancy.

**International Registered Report Identifier (IRRID):**

DERR1-10.2196/13566

## Introduction

Pancreatic cancer is the twelfth-most common cancer worldwide, but ranks fifth in its contribution to cancer-related deaths [1,2]. While the prognosis of most solid-organ cancers has improved over the last decade, the outcomes of patients with pancreatic cancer remain poor with an overall 5-year survival rate of 18% and 3.5% for patients with resectable and nonresectable disease, respectively [1,3]. This poor prognosis is partly explained by patients often presenting with advanced disease or distant metastases, due to the incipient nature by which pancreatic cancer develops and the absence of an effective screening tool [4,5]. Like pancreatic cancer, the other periampullary malignancies and extrahepatic cancers—herein collectively termed hepatopancreaticobiliary (HPB) malignancies—also have poor prognoses [6-8].

Due to the complex anatomy of the pancreas and biliary tract, the investigation of HPB malignancies requires multimodal approaches for diagnosis and staging. These tumors may involve local vascular structures and currently there is a lack of evidence regarding the optimum management of borderline and locally advanced tumors. Consequently, there is wide variability in the investigation and management of HPB malignancies between countries, but also on a national level [9,10]. It has been recognized that variability in the patient pathway can have a dramatic impact upon outcomes among these patients with regard to the time required to come to a diagnosis and referral to a specialist resectional center [11-15]. The need for better diagnostic pathways and faster access to surgery have recently been incorporated into the UK National Institute for Health and Care Excellence (NICE) guidelines for the diagnosis and management of pancreatic cancer [16]. Furthermore, the European Society for Medical Oncology recognized the rising number of deaths from pancreatic cancer in Europe and has also outlined recommendations for screening and diagnosis of pancreatic cancer [17].

In this paper, we describe the protocol of the Receipt of Curative Resection or Palliative Care for Hepatopancreaticobiliary Tumours (RICOCHET) study. This prospective study aims to define variations in diagnostic and management pathways for patients with suspected HPB malignancies, determine factors associated with these variations, and test the hypothesis that these variations have an impact on patient outcomes.

## Methods

This national, multicenter, prospective observational study will be coordinated and delivered by a cross-specialty, trainee-led research network in collaboration with surgeons, physicians, and allied health care professionals.

### Objectives

This study will define the pathways that patients with suspected HPB malignancies take from presentation to the completion of treatment, in terms of times between key diagnostic tests, multidisciplinary team (MDT) meetings, management of jaundice, treatments, and outcomes. Furthermore, it aims to define the variation in these practices and the potential effect of this variation in observed outcomes. The intention of therapy for patients with an HPB malignancy is determined by whether the primary lesion is deemed surgically resectable or not. The secondary objectives of the study are sectioned by intent of therapy (ie, resectable or nonresectable). The details of the primary and secondary objectives can be found in Table 1. Audit standards of the RICOCHET study are shown in Table 2. While patients will be analyzed by resectional status, outcomes from palliative management, which may occur concurrently, will also be collected. Therefore, referrals to a palliative care team, rates of palliative chemotherapy, and reviews by a clinical nurse specialist (CNS) have been included in our data collection.

In undertaking a cross-specialty national study, we aim to develop a lasting collaborative research network that will provide a framework for future clinical research.

**Table 1 table1:** Primary and secondary objectives of the RICOCHET^a^ study.

Objectives and outcomes				Outcome measures
**Primary objective: To describe the management pathways and 90-day outcomes for patients who are investigated with suspected resectable and nonresectable cancer of the pancreas, periampullary tissues, and the major bile ducts**				
	**Management pathway domains**			
		Presentation to secondary care		Presentation to outpatient clinic, emergency admission, referral from spoke center, incidental radiological finding, etc
		Principal care point		Whether first presentation was at a hub or spoke center^b^
		Utility of MDT^c^		Whether case discussed at MDT meeting Timing with reference to presentation and frequency
	**Investigation domains**			
		Imaging		Timing of imaging with reference to presentation Modality and frequency USS^d^, CT^e^, MRI^f^, and PET CT^g^
		Diagnostic tissue sampling		Timing of diagnostic sampling with reference to presentation Modality and frequency EUS FNA^h^, ERCP^i^, PTC^j^ brushings, and tissue biopsy
	**Intervention domains**			
		Biliary decompression		Utility: describing indication for decompression Modality: ERCP, PTC, or other Safety: decompression modality-specific complication rates Success rates as defined by successful biliary drainage^k^
		Neoadjuvant chemotherapy		Utility: rates of use Safety: chemotherapy-specific complication rates
		Nutritional supplementation		Utility of specialist nutrition team input: rates of referral Utility of pancreatic enzyme replacement: rates of prescription
	**Intention domains**			
		Curative surgery		Time from presentation to surgery Rates of completion of surgery with curative intent or awaiting surgery Histological staging Rates of adverse events
		Palliative and end-of-life care planning		Rates of referral to hospital or community palliative care team if appropriate Number of patients seen by a CNS^l^ Number of patients where ceiling of care and resuscitation status has been discussed
		Other outcomes		Number of inpatient days Number of unplanned admissions Death: time and cause
**Secondary objectives: resectable**				
	**Subgroup comparison of patients with obstructive jaundice who undergo preoperative biliary decompression versus patients who do not have decompression**			
		Decision making		Recording reasons why biliary decompression withheld in patient with obstructive jaundice
		Management pathway, investigation, intervention, and intention domains		Comparison of outcome measures, as in primary objective, between patients who did and did not undergo biliary decompression

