### Case Identification, Inclusion, and Follow-Up

Aspects of health care in the United Kingdom are modelled on a hub-and-spoke design, which arranges service delivery assets into a network consisting of a tertiary care provider, the hub, complemented by secondary care providers, the spokes. The hub offers a specialist service, including resection, whereas the spokes offer a more limited service, routing patients needing specialist treatment to the hub [23].

Adult patients with a newly suspected HPB malignancy will be identified and screened for inclusion at participating sites over a 90-day, case-identification period. A patient will be included according to one of the three inclusion criteria: (1) suspected malignant pancreatic lesion, (2) suspected periampullary lesion, or (3) suspected malignant biliary obstruction caused by a primary malignancy of the liver hilum or extrahepatic biliary tree (see Figure 1). Exclusion criteria include the following: less than 16 years of age, recurrent HPB malignancy, suspected secondary malignancy (ie, metastatic disease of an origin outside of the HPB anatomical area), and gallbladder or intrahepatic lesions. Cases will be identified at four nodes: MDT meetings, CNS referrals, from biliary decompression lists, and any remaining modes of referral, including through outpatient clinic and ward referrals (see Figure 2). Upon inclusion to the study, each patient’s management and investigative pathways will be charted from their initial relevant presentation to hospital care at the participating site. This *day zero* will be defined as the chronologically primary relevant attendance to the emergency department, outpatient clinic, discussion of the case at MDT where a diagnosis of malignancy was first considered, or the date of the radiological or endoscopic imaging that identifies an incidental finding of malignancy. Cases will be mapped by the outcome measures described in Table 1 for 90 days from *day zero*. For cases in which a patient’s care is moved between a spoke and hub center, data will be collected from site-specific *day zero* for the following 90 days. For the purpose of analysis, we will primarily assess 90-day outcomes from the first *day zero*. However, we may explore extended time points as part of an exploratory outcome analysis. The differences in treatment and outcomes of patients across centers (ie, hub or spoke) will be analyzed.

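### The resectable comparison groups patients by decompression received after day zero but counts outcomes from day zero, which builds immortal-time bias into death and surgery results

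*Protocol article*

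**What the plan says.** In the protocol article, Table 1 (Secondary objectives: resectable) sets up a "Subgroup comparison of patients with obstructive jaundice who undergo preoperative biliary decompression versus patients who do not have decompression". The content is a "Comparison of outcome measures, as in primary objective, between patients who did and did not undergo biliary decompression". The measures carried over from the primary objective include "Number of inpatient days Number of unplanned admissions Death: time and cause", and also time to surgery and completion of surgery.

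The clock is fixed under Case Identification, Inclusion, and Follow-Up. Day zero "will be defined as the chronologically primary relevant attendance to the emergency department, outpatient clinic, discussion of the case at MDT" where malignancy was first considered, or the date of incidental imaging. Decompression is not part of that definition. The same section states: "For the purpose of analysis, we will primarily assess 90-day outcomes from the first" day zero.

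On the choice to decompress, Table 1 adds "Recording reasons why biliary decompression withheld in patient with obstructive jaundice". The Statistical Analysis section leaves the techniques open and says nothing about the timing of exposure.

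**The concern.** Group membership is decided by an event that normally comes after the clock has started. To count as decompressed before surgery, a patient must be alive and not yet operated on when the procedure takes place. Two kinds of patient therefore fall into the comparison group by construction:

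- those who die while waiting for a planned decompression;
- those who go to surgery before it is done.

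The waiting time of decompressed patients, in which by definition they neither died nor had surgery, is credited to decompression. Adjusting for baseline covariates does not help, because the fault lies in how person-time is assigned.

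This is the first secondary comparison, and the study wants to test whether variation in practice affects outcomes and to inform a more standardized pathway. One table could show a survival benefit and a surgical delay that are both artefacts of the grouping.

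**Working it through.** **Plan's own figure.** The article gives no effect size, event rate or time to decompression for this comparison, so there is nothing to reproduce. Its only size figures are about 1835 cases (Sample Size) and a 15% potentially resectable share (Discussion): 0.15 × 1835 ≈ 275 patients. The jaundiced share is not given.

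**Assumptions (none is in the article).** Decompression has no effect on death or surgery. Times are exponential, and the death hazard is unaffected by surgery.

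- 90-day mortality m: 3 to 10%; λ = −ln(1−m)/90.
- Median wait to decompression w: 3 to 14 days; δ = ln 2/w.
- Median time to surgery s: 30 or 60 days, or no surgery; σ = ln 2/s or 0.
- Share planned for decompression p: 60%.

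**Formulas.** A patient is decompressed if planned and if the wait is shorter than the time to death, to surgery and to day 90.

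- A = δ/(δ+λ+σ) × [1 − e^(−90(δ+λ+σ))]; P(decompressed) = pA.
- B = (1−m) × δ/(δ+σ) × [1 − e^(−90(δ+σ))]; P(decompressed and dead by day 90) = p(A−B).
- Death risk: (A−B)/A in the decompressed; [m − p(A−B)]/(1−pA) in the others.
- S = σ/(σ+λ) × [1 − e^(−90(σ+λ))] is the overall probability of surgery by day 90. C = σ/(σ+λ) × [A − e^(−90(σ+λ))(1 − e^(−90δ))]. Surgery risk: C/A in the decompressed; (S − pC)/(1−pA) in the others.

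**Example 1: m = 10%, w = 7, no surgery.** λ = 0.001171, δ = 0.09902, A = 0.9882, B = 0.8999.

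- Decompressed: 0.0883/0.9882 = 8.9%.
- Not decompressed: (0.1 − 0.6 × 0.0883)/(1 − 0.5929) = 11.5%.
- Risk ratio 0.77; the true value is 1.

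**Example 2: the same with s = 60.** σ = 0.01155, A = 0.8861, B = 0.8059, S = 0.6191, C = 0.5157.

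- Death: 0.0802/0.8861 = 9.0%, against (0.1 − 0.0481)/0.4683 = 11.1%; risk ratio 0.82.
- Surgery by day 90: 0.5157/0.8861 = 58%, against (0.6191 − 0.3094)/0.4683 = 66%.

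**Range (p = 60%), decompressed vs not:**

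| m | w (days) | s (days) | Death by day 90 | Risk ratio | Surgery by day 90 |
|---|---|---|---|---|---|
| 3% | 3 | none | 2.9% vs 3.2% | 0.89 | – |
| 3% | 3 | 60 | 2.9% vs 3.2% | 0.90 | 62% vs 66% |
| 3% | 14 | none | 2.4% vs 3.9% | 0.61 | – |
| 10% | 3 | 30 | 9.6% vs 10.5% | 0.91 | 83% vs 86% |
| 10% | 7 | 30 | 9.1% vs 10.8% | 0.85 | 82% vs 87% |
| 10% | 14 | none | 8.0% vs 12.8% | 0.62 | – |
| 10% | 14 | 60 | 8.3% vs 11.5% | 0.72 | 55% vs 68% |

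Over the assumed ranges the death risk ratio runs from 0.61 to 0.91. With p = 80% the same formulas give 0.45 to 0.86.

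**Does time-updating remove it?** Yes. When the days before the procedure are counted as not decompressed, both rate ratios equal 1.00 in this model. A simulation over a wider grid (mortality 3 to 25%, waits 3 to 21 days, p of 60 or 80%) agrees. Grouped as the article words it, the death rate ratio is 0.38 to 0.92 and the surgery rate ratio 0.40 to 0.84. Time-updated, they are 0.98 to 1.02 and 1.00.

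**The case against.** The strongest reply is that this is a row in an objectives table, not an analysis specification. The techniques are left open, and an analysis plan that is not shown may treat decompression as time-updated. That stands as a condition: the bias follows if the comparison is run as worded. It does not dispose of the point, because the article itself fixes both the groups and the clock, and an open choice of technique changes neither. Elsewhere the article does anchor outcomes to the procedure: the 7- and 30-day survival standards in Table 2 run from decompression.

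Three further objections stand.

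- The size rests on inputs that the article does not give. At 3% mortality and a 3-day wait the gap is 0.3 percentage points. Even in all 275 potentially resectable patients, 0.003 × 275 ≈ 0.8, less than one death.
- Many of the compared measures, such as imaging modality, MDT use and nutrition referral, describe the pathway. They are not the time-to-event outcomes examined here.
- Who is decompressed depends on indication. That confounding could offset or reverse the immortal-time effect.

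A reader might infer that the grouping makes decompression look better throughout, including a spurious advantage in reaching surgery. The article does not support that. Because the groups are defined by preoperative decompression, early surgery removes patients from the decompressed group, so the surgery result is distorted the other way.

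**Conclusion.** The point holds, conditional on the comparison being run as worded. Grouping by decompression after day zero, with outcomes counted from day zero, biases death in favour of decompression and biases time to surgery and completion of surgery against it, when there is no true effect. Under the stated assumptions the death risk ratio is about 0.6 to 0.9, with a small absolute difference when waits are short and mortality is low. The direction for unplanned admissions and inpatient days was not calculated. The net direction of the reported contrast is unknown, because confounding by indication acts as well and cannot be sized from the article. The comparison should be corrected, but the article gives no basis for saying how large the error will be in this cohort.

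**What to change.** For the time-based outcomes (death, surgery, unplanned admissions), state one of the following:

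- **Time-dependent exposure.** Follow from day zero and count each patient as unexposed until the procedure date. Fix the status at surgery, since only preoperative decompression counts. Use cause-specific hazard models with death and surgery as competing events.
- **Landmark.** Name a day in advance, group patients by status on that day, and follow only those still alive and not yet operated on.
- **First recorded strategy.** Group by the initial plan, start follow-up at the decision date, and leave patients in their planned group. The field for reasons withheld helps, but the plan and its date must also be on record.

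Keep the did/did-not contrast as description only, and say that none of these options removes confounding by indication.

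The cost is slightly more analysis work. The Table 2 survival standards already need procedure and death dates, and time to surgery is a listed measure, so the first option should need no new data. A landmark drops early events, and grouping by plan dilutes the contrast somewhat where plans change.

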	**Subgroup comparison of patients who primarily attend a hub center compared to a spoke center**			
		Management pathway, investigation, intervention, and intention domains		Comparison of outcome measures, as in primary objective, between subgroups
**Secondary objectives: nonresectable**				
	**Subgroup analysis of cohort who undergo biliary decompression^k^**			
		Management pathway, investigation, intervention, and intention domains		As in primary objective, with intention to determine associations with adverse events and “other outcomes”
		Additional intention domain: palliative chemotherapy		Rates of starting palliative chemotherapy

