	**National research network development**			
		Promotion of collaborative research		Size of geographical region Number of sites in geographical regions Number of regional leads, local leads, and data collectors

^a^RICOCHET: Receipt of Curative Resection or Palliative Care for Hepatopancreaticobiliary Tumours.

^b^Hub-and-spoke design: network consisting of an anchor establishment, the hub, complemented by secondary establishments, the spokes.

^c^MDT: multidisciplinary team.

^d^USS: ultrasound scan.

^e^CT: computed tomography.

^f^MRI: magnetic resonance imaging.

^g^PET CT: positron emission tomography-computed tomography.

^h^EUS FNA: endoscopic ultrasound fine-needle aspiration.

^i^ERCP: endoscopic retrograde cholangiopancreatography.

^j^PTC: percutaneous transhepatic cholangiography.

^k^Successful decompression is defined as the successful deployment of a stent as stated on the latest procedure report.

^l^CNS: clinical nurse specialist.

^m^HPB: hepatopancreaticobiliary.

**Table 2 table2:** Audit standards of the RICOCHET^a^ study.

Audit standard		Standard compliance, %
Patients proceeding to surgery for pancreatic cancer should be found to have metastatic disease [9]		<25
For patients undergoing first biliary decompression, stent should be placed and cytology or histology taken where appropriate [18]		>80

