**Patient survival after biliary decompression in palliative disease**		
	7 days [19,20]	>90
	30 days [21]	>75
Ability to proceed to palliative chemotherapy in patients with unresectable malignancy [22]		25

^a^RICOCHET: Receipt of Curative Resection or Palliative Care for Hepatopancreaticobiliary Tumours.

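### Table 1 reports biliary drainage success, but its footnote counts only stent deployment; the same footnote on the nonresectable cohort heading leaves membership unclear

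*Protocol article*

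**What the plan says.** Table 1 of the protocol article, under the intervention domains of the primary objective, describes biliary decompression by indication, modality, safety and success. Modality is open-ended: "Modality: ERCP, PTC, or other". Safety is given as "Safety: decompression modality-specific complication rates". The success measure is "Success rates as defined by successful biliary drainage", and it carries footnote k.

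Footnote k, below Table 1, reads: "Successful decompression is defined as the successful deployment of a stent as stated on the latest procedure report".

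The footnote is used in one other place. Under the nonresectable secondary objectives it marks the heading "Subgroup analysis of cohort who undergo biliary decompression". The measures for that subgroup are those of the primary objective, and the aim is to find associations with adverse events and with the other outcomes, which include death.

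Two related places do not carry the footnote: the resectable comparison of patients with and without preoperative decompression in Table 1, and the audit rows in Table 2.

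**The concern.** The row names one event and the footnote defines another. The row speaks of drainage, for any modality. The footnote recognises only a stent, as recorded in the procedure report. A reader of the results would take the figure for the proportion of patients whose bile duct was drained, and it would not be that. Routes that drain without a stent would look worse than they are because of the definition alone. A stent that was placed but did not work would look like a good result.

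The second use of the footnote raises a separate question. A definition of success attached to a heading that names a cohort invites an analyst to ask whether success is a condition of entry. Two analysts could form two different cohorts from the same data, in the subgroup where adverse events and deaths after decompression are examined.

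**Working it through.** The article states no success rate, failure rate or cohort size for decompression, so there is no figure to reproduce. The check sets the definitions side by side.

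**Success measure.** Classify each patient who undergoes decompression by two facts, with shares that sum to 1:

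| | Bile drains | Bile does not drain |
|---|---|---|
| Stent deployed | a | b |
| No stent deployed | c | d |

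- Rate under footnote k: a + b.
- Rate that the row names (drainage): a + c.
- Error in the reported rate: (a + b) − (a + c) = b − c.
- Share of patients put in the wrong class: b + c.

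Three things follow.

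1. The overall error can go either way. If b and c happen to be equal, the overall rate is right while individual patients are still misclassified.
2. Among patients treated by a route without a stent, a = b = 0. The reported success is then 0%, whatever the value of c, so for these patients the error can only be downward.
3. The article does not list what the category of other modalities covers. An external percutaneous drain and a surgical bypass are examples supplied here of drainage without a stent. PTC with a stent is scored as success under the footnote, so the problem concerns unstented drainage and not PTC as such.

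**Cohort heading.** Compare the two possible readings with the rest of the article.

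- *Stented patients only.* The subgroup takes over the primary-objective measures, which include the success rate. In a cohort restricted to deployed stents that rate is (a + b)/(a + b) = 100% by construction, so the measure would carry no information.
- *All attempts.* The heading speaks of undergoing decompression, not of undergoing it successfully. Complications are recorded by modality with no restriction to successes. Table 2 takes patients undergoing a first decompression as the denominator and stent placement with sampling as the result, at a standard of >80%. The article therefore separates having the procedure from having a stent.

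The second reading fits better. What remains unexplained is why this heading carries the footnote when the resectable comparison, worded in the same way, does not.

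**The case against.** The strongest reply is that the footnote is an openly stated operational definition. Stent deployment can be read from a procedure report at every site, whereas functional drainage may not be recorded there. That is a fair reason to collect the stent measure. It is not a reason to call it drainage, or to apply it to modalities that need not involve a stent.

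It can also be said that Table 1 specifies modality-specific rates only for complications, and that no comparison of success between modalities is announced. This stands: the article does not promise such a comparison. The misclassification affects the overall success rate all the same, and any breakdown by modality would inherit it.

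A third reply is that categories of this kind belong in the data dictionary or the full protocol, which are not shown. That would answer a missing detail. Here the article states a rule, and the rule conflicts with the row to which it is attached.

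A reader might go further and infer that the footnote makes a stent the entry condition for the nonresectable cohort, so that failed attempts and their deaths drop out. The documents do not support this. The footnote defines only successful decompression, and the heading and its success measure point to all attempts. Exclusion is a possible reading of a badly placed marker and not a stated rule.

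A reader might also infer that survival against the 7-day (>90%) and 30-day (>75%) standards in Table 2 is flattered. Those rows, headed "Patient survival after biliary decompression in palliative disease", carry no footnote k, and Table 1 lists the audit standards as an objective separate from the subgroup. Nothing restricts their denominator to stented patients.

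**Conclusion.** The point holds for the success measure. Table 1 names successful drainage across all modalities and footnote k replaces it with stent deployment, so drainage without a stent counts as failure and a non-draining stent counts as success. The size is b − c in the notation above. It cannot be put into numbers, because the article gives neither share and any figure would be an assumption. The direction is certain only for unstented routes, where success is understated.

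The cohort question is a smaller matter: an ambiguity created by where the footnote sits, with the surrounding text favouring all attempts. Complication rates and deaths under the primary objective are not affected, and no effect on the Table 2 survival figures is shown.

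The conclusion rests on one assumption beyond the text, that some patients in the study are drained without a stent or have a stent that does not drain. The open modality category allows for the first.

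**What to change.** 1. In Table 1, keep the stent measure but label it as what it is: technical success (stent deployed).
2. Where success is reported across modalities, score drainage established by any route as technical success, whether by stent, external or internal-external drain, or bypass.
3. Remove footnote k from the nonresectable cohort heading. State that the cohort is all nonresectable patients with an attempted decompression of any modality, and analyse success or failure within it.

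The cost is a change of wording in Table 1 and minor recoding in the data dictionary, using procedure reports that sites already read. If the collection form holds only a yes-or-no entry for a stent, the reports of unstented patients would have to be read again. One limit remains: a procedure report may not show whether a stent went on to drain. The new label makes that limit visible but does not remove it.
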